### Sample size assumptions

In a previous study that utilized mobile phones for insulin titration intervention for subjects with type 2 diabetes, proportions of patients reaching optimal insulin dose within 12 weeks were 88% and 37% in the intervention and usual care arms, respectively [7]. In the present clinical trial, for both the intervention and control groups, we provide telephone counseling 1 week after patient education and allow telephone counseling if the blood glucose level does not meet the target level in both ICT-based intervention and conventional intervention groups. Therefore, the rate of reaching the primary endpoint of the control group is expected to be 55%, higher than that of the reference, and the estimated proportion of the intervention group that meets optimal insulin dose is 88%, which is similar to the reference. With these assumptions, a sample size of 38 subjects per group is needed with a two-sided alpha threshold of 0.05 with 90% power. We aimed to recruit 96 participants (48 per group) to allow for a dropout rate of 20% during follow-up (Samsung Medical Center, *n* = 76; Samsung Changwon Hospital, *n* = 20) [17].

### Data collection

### Demographic and medical survey

Demographic and medical information, including age, smoking and alcohol consumption, past and present medical history (e.g., hypertension, dyslipidemia), family history of diabetes, and diabetes medication including oral glucose-lowering agents and insulin, other concomitant medications within 6 months of registration for the trial, and any history of complications due to diabetes (macrovascular and microvascular complication) will be collected.

### Anthropometric and vital sign measurements

At visits 1, 3, and 4, height, body weight, blood pressure, and pulse will be measured, and a brief physical examination will be performed. Body composition examination will be performed by bioelectrical impedance analysis (Table 1).

**Table 1 Tab1:**
[figure not shown]
Study schedule

PHR: Personal health record

### Laboratory tests

At visits 1, 3, and 4, blood samples are collected after at least 8 h of fasting to determine fasting glucose, HbA1c, white blood cell count (WBC), hemoglobin, hematocrit, platelet count, total protein, albumin, globulin, blood urine nitrogen (BUN), creatinine, uric acid, total bilirubin, aspartate aminotransferase (AST), alanine transaminase (ALT), alkaline phosphatase (ALP), calcium, phosphate, total cholesterol, triglycerides, HDL cholesterol, and LDL cholesterol. At visit 1, a urine hCG test is performed as a pregnancy test in women with childbearing potential.

### Questionnaire for satisfaction with diabetes treatment and ICT-based centralized monitoring system

Subjects complete the DTSQ and the satisfaction questionnaire for the ICT-based centralized monitoring system to assess the impact of the intervention on the self-management of diabetes at visits 1, 3, and 4 [Additional file 2]. As the DTSQ has 2 versions, one assessing current status (DTSQs) and one assessing change (DTSQc), the DTSQs will be used at baseline (visit 1), visit 3, and endpoint (visit 4), and the DTSQc will be used at endpoint (visit 4).

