### Study design

This is a 24-week, open-label, randomized, multi-center ICT-based clinical trial conducted in two different university-affiliated hospitals, Samsung Medical Center and Samsung Changwon Hospital. There are three follow-up measures: baseline, post-intervention at week 12, and at week 24. Subjects diagnosed as T1DM, T2DM, and/or post-transplant DM who are initiating basal insulin or intensifying their insulin regimen to a basal-bolus regimen will be given education on insulin injection, dose adjustment, and prevention of hypoglycemia and will be provided a Bluetooth-enabled glucometer at visit 1 for screening. Subjects will receive instructions to measure daily glucose level using a home glucometer, to record insulin regimen and dose, complete the hypoglycemia diary in the application if blood glucose <70 mg/dL or a hypoglycemic event occurs, and to synchronize data so it automatically transfers to the system. Subjects who synchronized their information daily during a 1-week run-in period will be accepted into the clinical trial and randomly assigned to either the ICT-based intervention group or the conventional intervention group at a ratio of 1:1. After randomization during week 1, telephone counselling will be provided for re-instructing insulin dose adjustment and re-confirming participants’ use of the at-home measurement device and PHR applications (visit 2; televisit). Subjects in the ICT-based intervention group will receive algorithm-based feedback messages when their glucose levels are out of the target range, in addition to recording, saving, and sending their data to the server via PHR applications. Subjects in the conventional intervention group will only record, save, and send their data to the server via PHR applications, without feedback messages. Investigators will examine the saved health information, including level of blood glucose, insulin dose, details on hypoglycemia recorded in the hypoglycemia diary, food diary, and number of steps, transferred through the PHR applications. At each clinical visit, anthropometric parameters, current medication use including insulin dose and other glucose-lowering agents, vital signs, body composition, and a questionnaire assessing satisfaction with the investigation will be examined, and blood tests will be performed. Figure 1 shows an overview of the study.

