The secondary outcome will be the proportion of patients who reach HbA1c <7% without severe hypoglycemia (unrecoverable hypoglycemia without the help of others) at weeks 12 and 24. Other secondary outcomes include mean fasting blood glucose values for three consecutive days prior to weeks 12 and 24; levels of HbA1c at weeks 12 and 24; the proportion of patients having hypoglycemia (total, asymptomatic, daytime, nighttime, severe hypoglycemia, and coma/convulsions) at weeks 12 and 24; the number of steps taken during weeks 1–12 and weeks 13–24; recorded exchange unit by food group (grain, fish, vegetable, fat, milk, and fruit groups) in each breakfast, lunch, and dinner on 3-day food diary at weeks 12 and 24; daily insulin dose, body weight, and blood pressure at weeks 12 and 24; lipid profiles including total cholesterol, high-density lipoprotein (HDL) cholesterol, triglycerides, and low-density lipoprotein (LDL) cholesterol at weeks 12 and 24; body composition, including lean body mass and fat mass, at weeks 12 and 24; satisfaction evaluation by Diabetes Treatment Satisfaction Questionnaire (DTSQ) [13–16] and a questionnaire for ICT-based centralized clinical trial monitoring at weeks 12 and 24; the number of self-monitoring blood glucose measurements; the mean duration of medical consultations by doctors at the outpatient clinic; and the number and mean duration of telephone counselling by diabetes educators at weeks 12 and 24.

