### Run-in period

Subjects must examine level of blood glucose through a Bluetooth-enabled glucometer for a 1-week run-in period and synchronize the measured glycemic information to the PHR app for automatic transmission to the server at least once a day during that week. If synchronization is unsuccessful, subjects should use manual input to transfer data beyond the pre-planned frequency; otherwise, they will be considered as a screening failure.

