### Data analysis

All continuous variables will be presented as mean ± standard deviation, and categorical variables will be presented as frequency and proportion. For analyzing primary outcomes, the percentage of patients who reached the optimal insulin dose within 12 weeks is presented, and the difference between the two groups is compared using Pearson’s chi-square test or Fisher’s exact test if the frequency is low (<5). Differences are analyzed using Pearson’s chi-square test or Fisher’s exact test for categorical variables and Student’s t-test or Wilcoxon’s rank-sum test for continuous variables of secondary outcome variables. Comparisons between the two groups will be performed using a stratification analysis based on the use of pre-prandial insulin two or more times per day and each research institute. Prespecified subgroup analyses, including use of immunosuppressants (including steroids); type of DM; HbA1c >9%; use of pre-prandial insulin; aged over 65, 60, or 55; type of basal insulin; and stage of chronic kidney disease at baseline are performed. For handling missing data, last-observation-carried-forward (LOCF) imputation method would be performed.

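### The ICT-system satisfaction questionnaire is scheduled at screening, before any home use, and under the unrestricted LOCF rule that answer would stand as the week 12 and 24 score of patients who leave before visit 3

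*Protocol article*

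**What the plan says.** All references are to the protocol article.

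- **Timing of the form.** The section on the satisfaction questionnaires states: "Subjects complete the DTSQ and the satisfaction questionnaire for the ICT-based centralized monitoring system to assess the impact of the intervention" and continues "on the self-management of diabetes at visits 1, 3, and 4 [Additional file 2". One visit list serves both instruments. The next sentence gives visit 1 a baseline role for the DTSQ status version only. Study design and Data acquisition and evaluation also place a satisfaction questionnaire at every clinic visit.
- **What visit 1 is.** Under Study design, patients "will be provided a Bluetooth-enabled glucometer at visit 1 for screening". Home use comes next; the Run-in period section says "Subjects must examine level of blood glucose through a Bluetooth-enabled glucometer for a 1-week run-in period". Randomization is later still: "Subjects who synchronized their information daily during a 1-week run-in period will be accepted into the clinical trial and randomly assigned".
- **When the outcome is used.** Outcome variables lists "a questionnaire for ICT-based centralized clinical trial monitoring at weeks 12 and 24". The section on evaluating the stability of the monitoring also ties it to those two visits.
- **Missing data.** Data analysis gives one general rule: "last-observation-carried-forward (LOCF) imputation method would be performed". It exempts no variable and does not bar carrying a screening value forward.

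**The concern.** At visit 1 a patient has at most been shown the device and the app. Nobody has synchronized readings from home, and nobody has been allocated to receive or not receive feedback messages. Whatever the form records then, it is not experience of the system or an effect of the intervention.

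This would be harmless if the visit 1 answer were never analysed, since the outcome is defined only at weeks 12 and 24. The LOCF rule removes that protection. For a randomized patient who leaves before visit 3, the visit 1 answer is the only observation and so the last one. Followed literally, the plan enters it as that patient's week 12 and week 24 satisfaction. Part of each arm's reported satisfaction would then come from people answering before use, and the arms would be compared on a mixture of real and pre-use scores.

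**Working it through.** **1. The plan's own figures.** Inputs from Sample size assumptions: 55% against 88%, two-sided alpha 0.05, power 90%, dropout 20%.

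- Pooled mean proportion: (0.88 + 0.55)/2 = 0.715.
- n = [1.960 × √(2 × 0.715 × 0.285) + 1.282 × √(0.88 × 0.12 + 0.55 × 0.45)]² / 0.33² ≈ 37.2, rounded up to 38 per group.
- 38/(1 − 0.20) = 47.5, rounded up to 48 per group.

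Both stated figures reproduce and are not disputed. They supply the 48 and the 20% used below.

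**2. Who is affected.**

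| Patient | Last ICT-system answer | Week 12 and 24 value under LOCF |
|---|---|---|
| Fails run-in | visit 1 | none, not randomized |
| Randomized, leaves before visit 3 | visit 1, pre-use | pre-use answer at both |
| Leaves between visits 3 and 4 | visit 3, post-use | genuine week 12 answer, carried to week 24 |
| Completes | visit 4 | observed at both |

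Only the second row is a problem.

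**3. How many.** Let f be the share of dropouts who leave before visit 3. The article does not give f, so a range is assumed. The early-dropout fraction is k = 0.20 × f, and the number per arm is 48 × k.

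| f (assumed) | k | Patients per arm | Both arms |
|---|---|---|---|
| 25% | 0.05 | 2.4 | 4.8 |
| 50% | 0.10 | 4.8 | 9.6 |
| 75% | 0.15 | 7.2 | 14.4 |
| 100% (ceiling) | 0.20 | 9.6 | 19.2 |

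**4. Effect on the between-arm difference.** Under LOCF an arm's mean is (1 − k) × completers' mean + k × pre-use mean.

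- *Equal k, equal pre-use means, and leavers who would have shown the same between-arm difference as completers.* The pre-use terms cancel and the LOCF difference is (1 − k) × the true difference: 0.95 of it at k = 0.05, and 0.80 at k = 0.20.
- *Unequal k, no true difference between arms.* The LOCF difference (ICT minus conventional) is (post-use minus pre-use mean) × (k in conventional arm − k in ICT arm). With an assumed shift of 0.5 SD and early dropout of 5% (ICT) and 15% (conventional), this is 0.5 × (0.15 − 0.05) = 0.05 SD. Reversing the dropout rates, or the sign of the shift, reverses the sign.

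**5. Whether using observed scores alone repairs this.** Take assumed values on a 0 to 1 scale: completers 0.80, pre-use 0.50, leavers' true view 0.20, k = 0.20.

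- Truth: 0.8 × 0.80 + 0.2 × 0.20 = 0.68.
- LOCF: 0.8 × 0.80 + 0.2 × 0.50 = 0.74.
- Observed only: 0.80.

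Here the observed-only mean is further from the truth than LOCF. Removing the invalid value does not recover the missing view, so a sensitivity analysis is needed as well.

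**The case against.** **Unseen material.** The study schedule (Table 1) and Additional file 2 are not shown. Either might show that the ICT-system form is not given at visit 1, or that a differently worded form is used there. The shared visit list may also be a by-product of condensing the protocol into an article. This limits certainty, but the visit list is stated, and two other sections put a satisfaction questionnaire at every clinic visit. A form about expectations would still be wrong to carry forward as satisfaction.

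**LOCF detail belongs in the SAP.** Which variables the rule covers is often settled there, and the article does not expressly say that screening values are carried forward. That is fair. The point is narrower: the two statements, applied as written, produce an invalid value.

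**Stronger readings that the documents do not support.**

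- A reader might infer that the check of the system's validity and stability is compromised, because the Background names questionnaire-based evaluation as a means to it. The sections on stability and on economic evaluation show that this check mainly compares interview, questionnaire and record data with transmitted app data. Satisfaction is a further item there.
- A reader might infer that LOCF flatters the system because the least satisfied leave first. That needs pre-use answers to exceed leavers' true views, and nothing in the article shows it.
- A reader might infer that the visit 1 answer will be the baseline for a change score. No change score is listed for this form.

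**Conclusion.** The point stands as a minor one. As written, the plan collects an ICT-system satisfaction answer before the system has been used at home, and its LOCF rule would turn that answer into the week 12 and 24 score of every randomized patient who leaves before visit 3.

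The ceiling is 9.6 of 48 patients per arm, reached only if all planned dropouts leave that early; about 2 to 7 is the range if 25% to 75% do. The shrinkage of up to 20% holds only under the three conditions in the working. Outside them, neither the direction nor the size of the bias is known.

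The conclusion assumes that the visit list applies to the ICT-system form as it reads, and that LOCF is not restricted elsewhere. The visit 1 DTSQ is a legitimate baseline, since it concerns current diabetes treatment. The primary outcome, the sample size, and the comparison of interview data with app data are untouched.

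**What to change.** 1. In the section on the satisfaction questionnaires, separate the two visit lists: the ICT-system form at visits 3 and 4 only, and the DTSQ status version at visits 1, 3 and 4 as now. This matches the week 12 and 24 outcome and loses nothing the plan analyses. Bring Study design, Data acquisition and evaluation, and the schedule table into line.
2. In Data analysis, state that no ICT-system satisfaction answer given before use is carried forward or used as a baseline.
3. Analyse the observed week 12 and 24 scores, and report the number of early leavers and their reasons by arm.
4. Add a simple sensitivity analysis, for example assigning early leavers a low score.

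**Cost.** One fewer form at screening and a few lines of text. The real downside is that early leavers have no score, so an observed-only result may overstate satisfaction if they were the least satisfied. Items 3 and 4 make that visible but do not remove it.

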### Education on insulin injection, dose titration, and prevention of hypoglycemia

At the screening visit (visit 1), all subjects are given face-to-face education on insulin injection, dose titration, and prevention of hypoglycemia. The initial daily basal insulin dose will be 10 units per day or 0.1–0.2 units per kg of body weight. The initial daily basal insulin dose can be increased when the fasting blood glucose level is 250 mg/dL or more at initiation, but it should not exceed 0.3 units per kg per day. The initial pre-prandial rapid-acting insulin dose will be 4 units or 0.1 unit per kg or 10% of the basal insulin dose. For patients who have already used insulin before enrollment, they will start on their previous insulin dose and adjust from there. Subjects in the study are instructed to titrate their insulin dose based on the glycemic target of fasting glucose 80–130 mg/dL in the morning, for those who are under 65 years of age and do not have a history of severe hypoglycemia that cannot be recovered without help. The target of fasting glucose level 100–140 mg/dL in the morning will be applied for subjects with 1) history of severe hypoglycemia; 2) age ≥ 65 years; 3) duration of diabetes mellitus over 15 years; 4) decreased renal function (estimated glomerular filtration rate < 45 mL/min/1.73 m^2^); 5) BMI <18.5 kg/m^2^; 6) unawareness of hypoglycemia; 7) unpredictable changes in blood glucose level; and 8) difficulties understanding the education provided.

### Distribution and use of at-home measurement device and personal health record apps

For all subjects, at-home measurement device including a Bluetooth-enabled glucometer will be provided and instruction including use of the device, synchronization, and automatic transmission of data to the server will be provided.

### Run-in period

Subjects must examine level of blood glucose through a Bluetooth-enabled glucometer for a 1-week run-in period and synchronize the measured glycemic information to the PHR app for automatic transmission to the server at least once a day during that week. If synchronization is unsuccessful, subjects should use manual input to transfer data beyond the pre-planned frequency; otherwise, they will be considered as a screening failure.

### Interventions

#### Randomization

Educators provide telephone counseling after the 1-week run-in period. Before the telephone counseling, investigators check the synchronization of the at-home measurement device and the PHR application through the web page for administrators. For those who are suitable for the clinical trial based on daily synchronization, block randomization will be performed. The subjects will be randomly allocated to an intervention with ICT-based centralized monitoring or not, at a ratio of 1:1, per the Interactive Web Response System (IWRS). The randomization is stratified according to the research institute (Samsung Changwon Hospital: Samsung Medical Center = 20:76) and the use of pre-prandial insulin two or more times per day.

### Telephone counseling and re-introduction of intervention

At week 1, educators provide telephone counseling to all subjects to assess concomitant medication use or any adverse events and to re-instruct insulin dose adjustment and PHR apps. Subjects who are screening failures must return the at-home measurement device to the clinic. All participants are instructed to call the diabetes educator if the measured blood glucose level is <70 mg/dL more than once, or if the blood glucose level is not in the range of the glycemic target more than twice. Also, unscheduled visits to the clinic are available if a subject has one or more severe incidents of hypoglycemia (requiring other help for recovery) during the study period, hypoglycemia (<70 mg/dL) two or more times per week, or experiences fasting blood glucose >200 mg/dL three or more times in the morning and wants to see a doctor during weeks 1–12. Unscheduled visits to the clinic are also allowed for subjects who have difficulty in insulin dose adjustment, despite two or more unscheduled tele-visits. All subjects will record a 3-day food diary regarding the exchange unit for each nutrient group (e.g., grain, fish, vegetable, fat, milk, and fruit groups) in the breakfast, lunch, and dinner prior to visits 3 and 4.

### ICT-based intervention group

Subjects allocated to the ICT-based intervention group will be informed about algorithm-based feedback messages, and that a diabetes educator can call the subject if the feedback message is not checked more than once. The detailed algorithms of the feedback messages are available in the supplementary information [Additional file 3]. Push messages generated by the home monitoring system server will be displayed on the screen of the subject’s PHR apps. If the synchronized blood glucose level is <70 mg/dL, the hypoglycemia diary is activated automatically and can also be activated by a participant if he or she experiences symptoms of hypoglycemia. Whether hypoglycemic symptoms (e.g., cold sweating, severe hunger, shivering, and panic) have occurred, whether they occur during the night or sleep, and whether subjects need help to recover from hypoglycemia can be recorded in the hypoglycemia diary from PHR apps. Moreover, additional telephone consultation after the feedback message ‘Unscheduled tele-visit’ will be performed and recorded on the ‘Unscheduled tele-visit’ page of eCRF when diabetes educators check the transferred data on the administrator webpage daily and find the data meet the following criteria: 1) there is no record of blood glucose and insulin dose within 2 days after the feedback message; 2) the blood glucose and insulin doses recorded for 2 days after the feedback message do not follow the pre-informed instructions; and 3) hypoglycemia occurs, but the hypoglycemia diary is not recorded.

### Data acquisition and evaluation

For all subjects, at each clinical visit, anthropometric parameters, current medication use (including types of insulin and insulin dose), hypoglycemic events, vital signs, body composition, questionnaire for satisfaction with the investigation, and any adverse events are examined, and blood tests are performed. The mean duration of medical consultations by a doctor at an outpatient clinic and the number and mean duration of telephone counselling calls by diabetes educators are also evaluated. Prior to the post-interventional clinical visit at weeks 12 and 24, a clinical research coordinator (CRC) will check whether subjects continuously run and synchronize their PHR apps, the number of synchronizations, transmitted data of insulin dose, parameters regarding hypoglycemia and the 3-day food diary, and the measured number of steps taken during weeks 1–12 and weeks 13–24 in both intervention groups. For the ICT-based intervention group, the CRC will identify the types of algorithm-based feedback messages, whether subjects act on the feedback, and the recorded data from the hypoglycemia diary.

